**Social Support and Marital Satisfaction**		
Postpartum Support Questionnaire (PSQ) [84]	PSQ is a 34-item scale composed of four subscales for perceived social support assessment: material support, emotional support, informational support, and comparison support. Respondents are asked to score how important support is perceived to be and how much support is received.	Postpartum
Marital Life Areas Satisfaction Evaluation Scale (EASAVIC) [85]	The EASAVIC (Escala de Avaliação da Satisfação em Áreas da Vida Conjugal) is a 44-item self-administered scale that assesses five dimensions of functional relationship (instrumental components of the relationship) and five dimensions of romantic affects. Developed, tested and validated for the Portuguese population.	Pregnancy Postpartum
**Child-mother Attachment, Child Emotional Self-regulation and Cognitive Self-control**		
The Strange Situation Procedure	This task involves a sequence of eight 3-min episodes designed to place moderate although increasing levels of stress on infants (i.e., unfamiliar play room, interacting with a stranger, and two separations from the mother). Videotapes of infants’ attachment behavior during the Strange Situation Procedure will be scored by trained, reliable coders following the procedures developed by Ainsworth and colleagues [86]. Infants will be classified as either securely attached (B), insecure–avoidant (A), insecure–ambivalent (C), or disorganized–disoriented (D).	Postpartum
Postpartum Bonding Questionnaire (PBQ) [87]	PBQ is a screening tool for mother-child bonding impairment. Women are asked to rate how often they agree with several statements on their feelings or attitudes towards their child. It is composed of four subscales: impaired bonding, rejection and anger, anxiety about care, and risk of abuse. High scores indicate impaired bonding. Instrument validated for the Portuguese population [88].	Postpartum
Questionnaire on the Difference Imaginary Baby vs. Real Baby (QDIBRB) [89]	QDIBRB-30 screens for differences between mother’s prenatal and postnatal perceptions in three dimensions: child positive emotional expressions, mother’s fears about behavioral meaning, and child appealing behavior. Respondents indicate their agreement with each statement in a 5-point Likert scale ranging from completely disagree to completely agree. High scores indicate large differences between imaginary and real baby. Developed, tested and validated for Portuguese women.	Postpartum
Schedule of Growing Skills II (SGS-II) [90]	SGS-II is a screening tool for psychomotor development that considers nine areas: passive posture, active posture, locomotion, manipulation, visual, hearing and language, speech and language, interactive social, self-care social and cognition. Children are classified as having an adequate or delayed development. Instrument validated for the Portuguese population [91].	Postpartum
Toy Removal Task [92]	2-min toy removal episode preceded by 90 s of playing between mother and child. During removal and after returning the toy, mothers will be instructed to stay non-interactive and assume a neutral expression.	Postpartum
Object Permanence	Object permanence is one of the cognitive developmental milestones. This experiment involves hiding a toy from the child to assess if the child would look for it (ca. 8 months old) or retrieving the toy at location B even though it was previously hidden several times at location A (A-not-B experiment; ca. 12 months old).	Postpartum
Child–Adult Relationship Experimental Index (CARE-Index) [93]	The CARE-Index assesses mother–infant interaction from birth to about two years of age. Mothers and infants are videotaped for 5 min during an unstructured free play session. A standard set of age-appropriate toys are arranged on a quilt on the floor of a laboratory playroom and mothers are instructed to play with their infant as they usually do. The CARE-Index system focuses on seven aspects of the infant´s and mother’s interactive behavior: facial expression, verbal expression, position and body contact, affection, turn-taking contingencies, control, and choice of activity.	Postpartum

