## Abstract

Women are exposed to increased burden of mental disorders during the perinatal period: 13–19% experience postpartum depression. Perinatal psychological suffering affects early mother-child relationship, impacting child’s emotional and cognitive development. Return-to-work brings additional vulnerability given the required balance between parenting and job demands. The MAternal Mental Health in the WORKplace (MAMH@WORK) project aims to develop and evaluate the effectiveness of a brief and sustainable intervention, promoting (a) maternal mental health throughout pregnancy and first 12 months after delivery, and (b) quality of mother–child interactions, child emotional self-regulation, and cognitive self-control, while (c) reducing perinatal absenteeism and presenteeism. MAMH@WORK is a three-arm randomized controlled trial. A short-term cognitive-behavioral therapy-based (CBT-based) psychoeducation plus biofeedback intervention will be implemented by psychiatrists and psychologists, following a standardized procedure manual developed after consensus (Delphi method). Participants (*n* = 225, primiparous, singleton pregnant women at 28–30 weeks gestational age, aged 18–40 years, employed) will be randomly allocated to arms: CBT-based psychoeducation intervention (including mindfulness); psychoeducation plus biofeedback intervention; and control. Assessments will take place before and after delivery. Main outcomes (and main tools): mental health literacy (MHLS), psychological wellbeing (HADS, EPDS, KBS, CD-RISC, BRIEF COPE), quality of mother–child interaction, child–mother attachment, child emotional self-regulation and cognitive self-control (including PBQ, Strange Situation Procedure, QDIBRB, SGS-II, CARE-Index), job engagement (UWES), and presenteeism. Intention-to-treat and per-protocol analyses will be conducted; Cohen’s d coefficient, Cramer’s V and odds ratio will be used to assess the effect size of the intervention. MAMH@WORK is expected to contribute to mental health promotion during the perinatal period and beyond. Its results have the potential to inform health policies regarding work–life balance and maternal mental health and wellbeing promotion in the workplace.

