## 2. Materials and Methods

### 2.1. Study Design and Setting

This is an open-label, three-arm randomized controlled trial of pregnant women who will be followed throughout pregnancy (starting at 28–30 weeks of pregnancy) until 12 months postpartum. The MAMH@WORK project will be conducted at the Environmental Health Institute of Lisbon School of Medicine (ISAMB-FMUL), Portugal, with clinical data being collected at three primary health care units, three hospitals and in a network of private clinics (all part of the MAMH@WORK consortium).

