The RE-AIM (Reach, Effectiveness, Adoption, Implementation, and Maintenance) framework will be used to assess this evidence-based intervention in terms of its potential for translation and public health impact [68]. To assess the reach dimension of this project, the participation rate given as the proportion of invited pregnant women that accepted to participate in the intervention will be calculated. The effectiveness of the intervention will be assessed through a three-arm randomized controlled trial (Figure 1). The intervention group 1 will go through CBT-based psychoeducation sessions (including mindfulness e-training) by formally trained psychiatrists and psychologists; the intervention group 2 will benefit from the same CBT-based psychoeducation sessions (with mindfulness e-training) in addition to a biofeedback intervention; the control group will receive the care-as-usual from their health units. The development of a website for the project is planned and will include public and private areas. The public area will be accessible to the public and will contain information on mental health literacy, a description of the project’s objectives and its progress. Each participant allocated to the intervention arms will be provided with credentials to access her own private area. This area will contain personal, biomonitoring data (if applicable) and mindfulness e-training materials. Progressive Web Apps mimicking the website will be developed for smartphone use (Android and iOS).

Throughout the project, several physical and mental health outcomes will be measured and compared across groups. Since this intervention will be delivered by members of the research team, the adoption dimension (i.e., settings and staff that agree to deliver the intervention) does not apply in this case. However, the adequacy of the syllabus and a set of progress objectives (e.g., number of the psychoeducation intervention hours delivered, costs associated, and number of hours of online mindfulness exercises completed) will be used as a measure of its implementation. Finally, maintenance at both individual and setting levels will be measured at the last moment of data collection respectively by (a) the extent to which attendees maintain behavioral change after participating in the intervention and (b) the willingness of health unit managers to provide their users with this intervention.

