### 2.4. Data Collection and Variables under Study

Data collection will be performed through self-administered questionnaires, wearable devices for biomonitoring physiological signals (in association with a smartphone app), and direct observations of mother–child interactions. It will be conducted on five different moments (Figure 1): baseline (t_0_; 28–30 gestation weeks), one week after enrolment (t_1_; 29–31 gestation weeks), two weeks postpartum (t_2_), five months postpartum (t_3_), and twelve months postpartum (t_4_). Data collection will be performed by members of the research team. Women in the intervention group with biofeedback will wear a smartwatch to biomonitor several physiological signals combined with the use of a sleep analyzer device (for details, see Table 1). Both devices will communicate through Bluetooth with a datahub and send physiological data to the supplier’s cloud. The server will communicate on a regular basis, via a secure oAuth2 authentication method, with the supplier’s cloud and retrieve all data to be stored in a relational database including wearables-collected information, questionnaires filled in by the participants and health data gathered by healthcare professionals. Health indices computed out of these data will be made available to participants in their website/app private areas, alongside trend graphics and other simple although insightful data visualizations of relevant information such as sleep pattern, accelerometry, pulse rate, pulse rate variability, among others. The system to be developed will also support the project throughout its course, namely by generating reports on its evolution (e.g., successful contacts), listing scheduled contacts, and asking participants to fill in questionnaires, among others.

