Strategies to reduce attrition during the experimental period will be implemented. At recruitment, pregnant women will be provided with detailed information about the project, including the objectives and participant’s role in the study. During post-allocation period, referrals to other healthcare professionals will be performed as necessary, and the required logistic support for data collection will be provided, such as scheduling suitable data collection appointments [69]. Reminders will be sent to enrolled women one week before the scheduled date of each data collection moment. Women in the intervention group with biomonitoring of physiological signals will receive tailored health-related information based on data collected through wearable devices (biofeedback), whereas women in both the control and intervention arms will receive general health information via a smartphone app (also accessible in the private area of the project’s website). This app will be developed specifically for MAMH@WORK project and will be available for download by all women enrolled in the study. It will mirror information available at the website and facilitate communication between the research team and participants. 

The main outcomes that will be used to assess the effectiveness of the intervention are women’s psychological wellbeing (mood disorders and anxiety disorders, assessed by the Hospital Anxiety and Depression Scale/HADS and by the Edinburgh Postnatal Depression Scale/EPDS), subjective wellbeing (Self-Report of Happiness), quality of mother–child interactions (assessed by the CARE-Index) and child-mother attachment (assessed by the Strange Situation Procedure and by the Postpartum Bonding Questionnaire/PBQ). Secondary outcomes include child emotional self-regulation and cognitive self-control; women’s job engagement and presenteeism; and women’s physiological signals (pulse rate, pulse rate variability, and sleep patterns).

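### In an open-label trial, nothing requires the coders of the two video-rated main outcomes to be masked to arm

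*Protocol article*

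**What the plan says.** Section 2.1 sets the masking status once, for the whole trial: "This is an open-label, three-arm randomized controlled trial of pregnant women". No exception follows there or elsewhere for coders, assessors or analysts.

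Section 2.4 lists the main outcomes. Two are rated by an observer: quality of mother–child interaction (CARE-Index) and child–mother attachment (Strange Situation Procedure). The rest of that list (HADS, EPDS, the happiness item and the PBQ) is self-report.

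Table 1 describes both observer-rated measures as video-recorded. On the Strange Situation it says that the tapes "will be scored by trained, reliable coders" who follow a published method, with infants placed in one of four attachment classes. On the CARE-Index it says "Mothers and infants are videotaped for 5 min during an unstructured free play session" and lists the aspects of behaviour to be judged. It does not say who scores the recording or what is required of them.

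On staffing, Section 2.3 reads "Since this intervention will be delivered by members of the research team", and Section 2.4 reads "Data collection will be performed by members of the research team".

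**The concern.** Both measures depend on judgement: an attachment class in one case, and ratings of such things as affection, control and turn-taking in the other. A rater who knows the arm can lean towards the expected result without intending to. The content of the intervention adds to this. According to Section 2.3, the manual covers mother–child interaction and secure attachment, and the sessions use role play and case discussion of such interactions. The team therefore teaches what the videos are scored on.

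The women know their arm, so masking cannot protect the self-reported main outcomes. The two video measures are the ones in the Section 2.4 list that it can protect. If that is not required, the trial gives up its best safeguard for the mother–child results. Requiring reliable coders does not replace masking: two coders who both know the arm can agree closely and share the same lean.

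**Working it through.** **Reading the text.** The plan gives no figure to reproduce, so the first check is what it says about masking and coding.

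| Question | Strange Situation | CARE-Index |
|---|---|---|
| Main outcome in Section 2.4? | Yes | Yes |
| Recorded on video? | Yes (Table 1) | Yes (Table 1) |
| Coder training and reliability stated? | Yes | No |
| Coders masked to arm? | Not stated | Not stated |
| Coders separate from session leaders? | Not stated | Not stated |

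Section 2.2 adds that trained researchers open the allocation envelopes. Knowledge of the arm is thus present within the team, and no rule separates that knowledge from video scoring.

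**Illustrating the size.** Inputs from the article: significance level 0.05 (Section 2.5; taken here as two-sided, which is not stated) and n = 53 per arm (Section 2.2, minimum sample size). Everything else is assumed. There is no true effect, one intervention arm is compared with control, and a simple two-sample normal approximation stands in for the planned mixed model.

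*Continuous CARE-Index score.* Let b be the shift, in SD units, that knowledge of the arm adds in the intervention arm. The chance of a significant result is

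P(|Z + b·√(n/2)| > 1.96), with √(53/2) = 5.148.

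- b = 0.1: b·√(n/2) = 0.515, result 8.1%
- b = 0.2: 1.030, result 17.7%
- b = 0.3: 1.544, result 33.9%

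*Secure versus insecure attachment.* Let p1 be the true secure rate in both arms (assumed 0.5, 0.6 or 0.7) and m the share of insecure infants that coders move to secure in the intervention arm only. Then

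- p2 = p1 + m(1 − p1), Δ = p2 − p1, and p̄ is the mean of p1 and p2
- SE0 = √(2p̄(1 − p̄)/n) and SE1 = √((p1(1 − p1) + p2(1 − p2))/n)
- error rate = Φ((Δ − 1.96·SE0)/SE1) + Φ((−Δ − 1.96·SE0)/SE1)

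Example with p1 = 0.5 and m = 0.20: p2 = 0.60, Δ = 0.10, SE0 = 0.0966, SE1 = 0.0962, result 17.8%.

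| Share moved (m) | p1 = 0.5 | p1 = 0.6 | p1 = 0.7 |
|---|---|---|---|
| 5% | 5.8% | 5.5% | 5.3% |
| 10% | 8.1% | 7.1% | 6.3% |
| 20% | 17.8% | 13.7% | 10.6% |

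*Smaller sample.* If the 40% attrition named in Section 2.2 is applied to the 75 enrolled per arm, 75 × 0.60 = 45 remain. The continuous figures then become 7.6%, 15.8% and 29.6%, which does not change the picture.

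**The case against.** The strongest reply is that the article is silent on coder masking and that silence in a condensed article is not a flaw. Who codes which tape and how files are labelled may stand in the full protocol or a coding manual, neither of which is shown. The term open-label can describe the women and therapists, who cannot be masked in a group programme, without settling how tapes are coded later.

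Much of this stands. A reader might infer that the coders will know the arm, or that session leaders will score their own participants. The text supports neither. Sections 2.3 and 2.4 both speak of research-team members but do not say that they are the same people, and Table 1 names coders as a role of their own. The overlap is not excluded, but it is not planned either.

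Two limits on scope also stand. The training and reliability requirement is written for the Strange Situation only. And these are the only observer-rated main outcomes in the Section 2.4 list, but the Abstract's list is wider ("including PBQ, Strange Situation Procedure, QDIBRB, SGS-II, CARE-Index"): it places child self-regulation among the main outcomes, which Section 2.4 makes secondary, and names the SGS-II, which the Section 2.4 list omits.

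The reply does not remove the point. The article does address the subject: it declares a masking status for the trial and sets coder qualifications for a main outcome. Followed as written, those statements allow a person who knows the arm to score the tape.

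**Conclusion.** The point holds as an avoidable risk of rating bias in the two observer-rated main outcomes of Section 2.4. The gap is wider for the CARE-Index, where no coder requirement is given.

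The documents do not establish that bias will occur or how large it would be. It would go too far to say that a positive mother–child result could not be told apart from rater expectation. The figures are illustrations under assumed shifts: about 8%, 18% or 34% instead of 5% for a continuous CARE-Index score shifted by 0.1, 0.2 or 0.3 SD, and about 5–6%, 6–8% or 11–18% for attachment if 5%, 10% or 20% of insecure infants are moved to secure in one arm. The SD-shift figures should not be applied to the four-category attachment class. Small leanings matter little for attachment; larger ones would matter for both outcomes.

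The change is worth making because the recordings are already planned and masked scoring removes the arm-dependent part of this error. If the full protocol already requires masked coding, one sentence in the article settles the matter.

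**What to change.** State in Sections 2.1 and 2.4 that participants and therapists are unmasked, but that the Strange Situation and CARE-Index videos are:

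- stored under codes that do not reveal the arm;
- scored in batches that mix the arms;
- scored by coders masked to arm who delivered no sessions to the woman on the tape.

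Extend the trained-and-reliable requirement in Table 1 to the CARE-Index coders.

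The cost is file relabelling and somewhat less flexible coder scheduling; no extra visit is needed. One practical point has to be settled before filming: women in the biofeedback arm wear a smartwatch (Section 2.4), so care is needed that it does not reveal the arm on film. The change is confined to these two measures. Table 1 does not say that the toy removal and object permanence tasks are recorded, and this point does not ask for that.

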**Work** **–** **life Balance**		
The Utrecht Work Engagement Scale (UWES) [94]	UWES-17 is a three-dimensional scale that assesses vigor, dedication and absorption. Respondents are asked to score several emotions on a 7-point frequency scale. High scores indicate high engagement levels. Instrument validated for the Portuguese population [95].	Postpartum
Work–Family Balance Scale (WFB) [96]	WFB is a 5-item scale that assesses the extent to which women were able to balance work and their family life. High scores indicate good ability to balance work and family life demands.	Postpartum
Presenteeism questions of the World Health Organization’s Heath and Work Performance Questionnaire (HPQ) [97]	These questions are part of the full HPQ and measure the actual performance versus possible performance. High scores indicate low amount of lost performance, i.e., low presenteeism.	Postpartum
Self-reported absenteeism	Self-reported absenteeism is measured by asking individuals if they have missed work in the last year, how many days and what was the reason for that.	Postpartum
**Biomonitoring of Physiological Signals**		
Pulse rate (PR) Pulse rate variability (PRV) Body motion generated by the ejection of the blood at each cardiac cycle (Ballistocardiography, BCG) Peripheral capillary oxygen saturation (SpO_2_) Sleep patterns (SP) Physical activity (PA) tracking and sleep-time movement tracking Electrocardiogram (ECG)	PR, PRV SP, BCG, and PA will be monitored using a Hybrid Smartwatch. The Hybrid Smartwatch combined with the Sleep Analyzer will allow sleep-stage characterization. A sleep score based on six factors is also calculated: sleep duration, sleep regularity, time to sleep, sleep depth, frequency of sleep interruptions, and time to get up. Women will be invited to ask for an ECG once a week using the Hybrid Smartwatch.	Pregnancy Postpartum
